### Limitations of the study

We must consider that some older adults’ smartphones may be stolen, lost or damaged. This study will register any smartphone losses, and in this case, we will ask the older adult if they can continue in the study with another smartphone or if they will have to leave the study. In the last case, we will have to recruit another older adult meeting the inclusion criteria.

The smartphone may run out of battery during the listening of the poems. To minimize this inconvenience, older adults will be warned about this possibility in the “Induction and installation of the application” step (see Fig 4), and they will be encouraged to ensure that smartphones are always charged during the use of the audiobook application.

The literary genre chosen on this occasion (poetry) might not be the one preferred by most older adults participating in the study. At the end of the study, we should ask them and introduce other genres in another version of the audiobook application.

The resurgence of COVID-19 in Chile could make it necessary to extend the recruitment period for older adults, and also increase the total time budgeted for the study.

Finally and considering the above, older adults could be reluctant to participate in the study or meet with researchers in person, in which case we will opt for an online modality, either during recruitment, during follow-up, or when answering the questionnaires.

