### Design

A quasi-experimental study will be conducted during the second quarter of 2024 to assess the improvement in the well-being perception of older adults and the usability of an audiobook mobile application. This design is based on the desire to reduce ethical considerations (ethical problems of randomizing patients), avoid data contamination, and offer a more cost-effective and feasible approach for implementing this research [25–27]. In this study, participants will be compared with themselves at the beginning and at the end of the intervention, that is, a pretest/posttest with a single group.

Fig 4 shows the study protocol’s flow diagram. The first stage at the top corresponds to recruiting community-dwelling older adults, to be done at a community center (recruitment will begin at the end of April 2024 and be completed at the end of May 2024) by two of the researchers ([name], [name]). With the older adults who agree to participate in the study, we ([name], [name]) will do the second stage (screening), which consists of determining who can participate in the study by applying the inclusion and exclusion criteria (third stage). Before starting the intervention, participating older adults must accept and sign a written consent (fourth stage). Some of them may refuse to participate in the study and thus be excluded from it (fifth stage). Then, a baseline (sixth stage) will be established by applying standardized and validated tests to the participating older adults, who will then have an induction session, in which the three researchers will participate ([name], [name], [name]), to install the application on their smartphones, learn how to use the application and get answers to any questions they might have (seventh stage). In the intervention (eighth stage), the participants will use the application for four weeks (during June 2024), with a follow-up at 2 weeks (ninth stage) to be performed by two of the researchers ([name], [name]). After these four weeks of application use, the older adults will be evaluated through standardized tests (tenth stage). Finally, the data obtained from the questionnaires and from using the audiobook itself will be analyzed (eleventh stage).

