### Statistical analysis

For data analysis, a single database will be created with the results obtained from the application of the questionnaires, the older adults’ sociodemographic characterization, and the information collected automatically by the application.

Subsequently, descriptive statistics will be used for univariate and bivariate frequency analysis which will consider measures of central tendency (mean and standard deviation) to describe the characteristics of the sample and the questionnaire results.

Then, the study hypothesis will be carried out using a multivariate linear regression in order to characterize the well-being variable at the end of the intervention, controlled by the initial well-being, and by sociodemographic variables, usability and frequency of use.

We will explore if the covariates play a role of confounding effects and/or modifiers in the relationship between the initial and the final well-being score. The specific model is assumed to be a Generalized Linear Model, for normal distribution and identity link. Data processing and analysis will be performed using the IBM SPSS Statistics for Windows, Version 28.0 (IBM Corp. Released 2021, Armonk, NY, USA).

Data analysis will be performed under an intention-to-treat (ITT) approach by a researcher blinded to the study group. The multiple imputation technique [36] will be applied using the predictive mean matching method to handle missing data and ensure the inclusion of all participants in the analysis.

The proposed statistical model is summarized as follows:
$$\begin{array}{c} \begin{array}{c} B_{final}=a_{0}+b\left(B_{initial}\right)+b\left(frec\right)+b\left(usability\right)+b\left(gender\right)+b\left(other\;dem\right) \end{array} \end{array}$$
where

*B*_*final*_ : Final well-being score.*a*_0_ : Intercept.*b*(*B*_*initial*_) : Slope associated with initial well-being.*b*(*frec*) : Slope associated with the application’s frequency of use.*b*(*usability*) : Slope associated with the application’s evaluated usability.*b*(*gender*) : Slope associated with the participants’ gender.*b*(*other*
*dem*) : Slopes associated with other confounding demographic variables or relevant modifying effects.

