### Ethical considerations

The Scientific Ethics Committee of the Concepción Health Service in Concepción, Chile, approved this study on May 13th, 2021 (code CEC-SSC:21–01-06).

The researchers declare compliance with the Good Clinical Practices established by the Government of Chile. Furthermore, the research will ensure compliance with Law 20,584 regarding the Rights and Duties of patients (Ley 20,584 de Derechos y Deberes de los pacientes, in Spanish) and the ethical norms of the Declaration of Helsinki.

Participation of older adults in this research will be voluntary: they may withdraw at any chosen time, without any harm to them. The above will be stated in the informed consent form, which will be first presented verbally to the participants. Then, they will be asked to voluntarily sign a written copy, having previously received all relevant information about the process and objectives of the study.

Participants will not receive any direct benefit, reward, or economic compensation of any kind for participating in this study. Furthermore, the results will be made available to them.

The research team will protect each participant’s information, privacy and confidentiality. Data obtained will only be used to fulfill the objectives of this study. One of the researchers ([name]) will be in charge of safeguarding both the data obtained through the application and those obtained from the applied questionnaires. Once the research has finished, the data will be stored on a USB storage device for two years. It will be safely kept in a locked drawer in the office of the responsible researcher ([name]), who has sole access to it in the Department of Speech, Language, and Hearing Sciences, Universidad de Concepción, Chile.

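### The replacement rule after smartphone loss is not reconciled with the promised ITT analysis of all participants and loses exit outcomes needlessly; separately, a single-group study cannot have a group-blinded analyst.

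*Protocol article*

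**What the plan says.** **Leaving and replacement.** For a stolen, lost or damaged phone, Limitations of the study states that "we will ask the older adult if they can continue in the study with another smartphone or if they will have to leave the study". It continues: "In the last case, we will have to recruit another older adult meeting the inclusion criteria". No replacement rule is given for other withdrawals. Ethical considerations says only that "they may withdraw at any chosen time, without any harm to them".

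**Analysis set.** Statistical analysis states: "Data analysis will be performed under an intention-to-treat (ITT) approach by a researcher blinded to the study group". Multiple imputation by predictive mean matching is to be used "to handle missing data and ensure the inclusion of all participants in the analysis".

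**Design and calendar.** Design describes participants compared with themselves, "that is, a pretest/posttest with a single group". It says that "recruitment will begin at the end of April 2024 and be completed at the end of May 2024", and it places the four weeks of app use in June 2024.

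**Sample size.** Recruitment plans 60 people from a pre-post difference of 1.24, a standard deviation of 3.4, power 0.8 and error probability 0.05.

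**The concern.** Two separate matters meet in the analysis paragraph.

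The first is who is followed and analysed. An ITT analysis of all participants needs outcomes from everyone who started, whether or not they kept using the app. The phone rule instead takes a person out of the study because of a lost device and brings in someone else. If the newcomer fills the leaver's place, the analysed 60 are people who kept a working phone. If the leaver is kept by imputation, the missing score is drawn from the observed scores of people who stayed. In both cases a real answer that could have been collected is replaced by information from others. There is no control arm in which similar losses might offset this.

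The second is the blinding statement. It tells readers that a safeguard is in place, although the design offers nothing to be blinded to.

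**Working it through.** **1. Does the target of 60 allow for dropout?** Inputs from Recruitment: difference 1.24, SD 3.4, power 0.80, error probability 0.05. Sidedness is not stated; two-sided is assumed because it reproduces the figure.

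n = [SD × (z₀.₉₇₅ + z₀.₈₀) / difference]² = [3.4 × 2.8016 / 1.24]² = 59.01, rounded up to 60.

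The exact paired t calculation gives 61; a one-sided test gives 47. So 60 is the bare number needed with outcomes, with nothing added for losses. With 60 enrolled and no replacement, paired t power on observed cases is 0.79 with all 60, 0.77 with 57 and 0.75 with 54. That explains why a replacement rule is there, and it makes substitution to hold the number at 60 a likely reading.

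**2. What happens to the leaver's data?** Limitations of the study says the person leaves and another is recruited. Statistical analysis says all participants are included by imputation. Neither section says whether the leaver stays in the analysis set or whether the newcomer is a 61st person. Two readings remain:

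- *Added:* the leaver is imputed and the newcomer is extra. This is compatible with ITT.
- *Substituted:* the leaver drops out of the 60. This is not.

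**3. Is the missing outcome avoidable?** The exit outcome is Part B of the well-being questionnaire. Intervention places it at a meeting at the rehabilitation center, and Data collection procedure has documents completed on paper. Neither needs the participant's smartphone. Phone loss ends app use, and it may lose usage records not yet sent to the server, but it does not stop anyone answering Part B.

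**4. Does a replacement fit the calendar?** Recruitment ends at the end of May and the four weeks fall in June. June has 30 days and four weeks are 28, so someone starting after 3 June cannot finish within the month. A person recruited because a phone was lost during the intervention therefore falls outside the recruitment window and, except in the first days, outside the intervention period.

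**5. How large could the effect be?** The documents give no leaving rate, so this is an illustration only. Assume that stayers gain 1.24, that leavers gain nothing, and that k of 60 leave. The analysis reports 1.24; the mean over the 60 is 1.24 × (60 − k)/60; the overstatement is 60/(60 − k) − 1.

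| k leaving (of 60) | Mean over the 60 | Overstatement |
|---|---|---|
| 1 | 1.22 | 1.7% |
| 3 | 1.18 | 5% |
| 6 (10%) | 1.12 | 11% |
| 12 (20%) | 0.99 | 25% |
| 18 (30%) | 0.87 | 43% |

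The result is the same for substitution and for imputation that treats leavers like stayers. The table thus shows what is at stake in losing the exit score. It does not measure the replacement rule on its own.

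**6. Blinding.** Statistical analysis has the analyst blinded to study group; Design has "a pretest/posttest with a single group". With no allocation there is no group label to hide.

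**The case against.** A reader might infer that replacement flatly contradicts ITT. The article does not support that: it never says that leavers' data are dropped, and the imputation sentence can be read as keeping them while the newcomer is added. This objection stands, and it makes the point one of unreconciled rules.

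A reader might also extend the rule to everyone who leaves. It covers only irreplaceable phone loss, and ordinary withdrawal carries no replacement rule.

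A reader might take the lower rows of the table, 11% to 43%, as the size of the bias. They need six to eighteen such losses in four weeks and exactly zero gain in each leaver. Theft or damage is not obviously related to response, and a leaver may have used the app for some time. The 1.24 comes from a cited mental health outcome and is not on the scale of this study's questionnaire, and the planned analysis is a regression of the final on the initial score, not a mean change. These objections stand.

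On timing, Results speaks of approximately one month of recruitment and of data collection complete by July, so there is some slack for questionnaires. That does not bring a June recruit within the dates in Design. The only stated ground for extending recruitment is COVID-19.

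The online option in Limitations of the study is meant for people reluctant to take part or to meet in person. Completion on paper at the center is therefore the firmer basis for calling the loss avoidable.

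Finally, the blinding phrase conflicts with the single-group design, not with ITT. It is a defect of its own.

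**Conclusion.** The point holds in limited form and should be corrected. As written, the rule takes people out of follow-up for a reason that does not prevent them from giving the outcome, and it leaves open whether their replacements are added or substituted. Substitution is likely, though not stated, given a target with no dropout allowance. The rule also does not fit the recruitment and intervention dates.

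The size of any bias is unknown. Under the zero-gain assumption it is about 1.7% of the mean change for one such case in 60 and about 5% for three, with larger values only at higher assumed leaving rates.

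The blinding statement is wrong as written, whatever an unseen analysis plan may add.

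**What to change.** 1. In Limitations of the study, state that participants who lose their phone or stop using the app stay in the study for the exit well-being questionnaire, answered in person on paper, by phone or online.
2. In Statistical analysis, state that everyone enrolled stays in the analysis set and that any late entrant is added and never substituted. Reconcile late entry with the dates in Design.
3. Optionally, add one sensitivity analysis that sets missing final scores to no change.
4. Delete the phrase about blinding to study group and say that the analysis is unblinded. Masking the pre and post labels would not rescue the claim: Outcome measures gives 6 questions in Part A and 12 in Part B, and the regression must know which score is initial.

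The cost is a few sentences of protocol text, a small number of extra questionnaires and, if chosen, one further model run.

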### Ethical considerations

The Scientific Ethics Committee of the Concepción Health Service in Concepción, Chile, approved this study on May 13th, 2021 (code CEC-SSC:21–01-06).

The researchers declare compliance with the Good Clinical Practices established by the Government of Chile. Furthermore, the research will ensure compliance with Law 20,584 regarding the Rights and Duties of patients (Ley 20,584 de Derechos y Deberes de los pacientes, in Spanish) and the ethical norms of the Declaration of Helsinki.

Participation of older adults in this research will be voluntary: they may withdraw at any chosen time, without any harm to them. The above will be stated in the informed consent form, which will be first presented verbally to the participants. Then, they will be asked to voluntarily sign a written copy, having previously received all relevant information about the process and objectives of the study.

Participants will not receive any direct benefit, reward, or economic compensation of any kind for participating in this study. Furthermore, the results will be made available to them.

The research team will protect each participant’s information, privacy and confidentiality. Data obtained will only be used to fulfill the objectives of this study. One of the researchers ([name]) will be in charge of safeguarding both the data obtained through the application and those obtained from the applied questionnaires. Once the research has finished, the data will be stored on a USB storage device for two years. It will be safely kept in a locked drawer in the office of the responsible researcher ([name]), who has sole access to it in the Department of Speech, Language, and Hearing Sciences, Universidad de Concepción, Chile.

## Results

As mentioned, recruitment will start at the end of April 2024, and we expect to enroll an estimated number of 60 older adults. Recruitment should last approximately one month, and a follow-up will be done in June 2024. Finally, the data collection should be complete by July 2024.

If the results confirm our hypothesis, i.e., that listening to audio of poems using a mobile application improves the perception of well-being of older adults, we could test the effectiveness of this intervention considering other aspects: (1) adding other literary genres (or subgenres) to the audiobook such as drama, fiction and nonfiction; (2) incorporating a greater number of books for each genre; (3) carrying out the intervention with another population, such as people in another age range, or blind people, among others.

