### Objective, research question and hypothesis

The goal of this 4-week quasi-experimental study is to assess the impact of an audiobook mobile application on the well-being perception of older adults belonging to a Community Rehabilitation Center (CRC) at Concepcion, Chile, and to evaluate the usability of the mobile application designed for this population.

Our research question is the following: Does listening to audio poems using a mobile application improve the perception of well-being of the older adults who go to the CRC at Concepción?

Finally, our hypothesis is that using a mobile application that allows listening to poems produces a positive change in older adults’ perception of well-being.

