### Recruitment

The participants will be recruited from the Community Rehabilitation Center at Concepción, Chile. We estimated our sample size considering a pre-post difference of 1,24 points on the mental health outcome [28] and a potential standard deviation of 3,4. Thus, we planned for a sample size of 60 individuals [29] with a continuous response variable measured pre-post intervention to be able to reject the null hypothesis that the response difference is zero with power 0,8 and an error probability of 0,05. The sampling technique will be non-probabilistic and will be used for the convenience of the study.

Recruitment flyers will be posted on the walls of the CRC to make an open call to all people over 60 years of age being treated at that place. Furthermore, group meetings scheduled by the researchers ([name], [name]) will be held at the CRC offices to invite older adults to participate in the research. Older adults interested in the study will register by giving their name and telephone number, and will be contacted later by the researchers ([name], [name]).

Older adults interested in participating in the study will be contacted by telephone. Then, the study, the objectives of the research and the strategy to be used in the study will be explained to them in a concise and precise way. Furthermore, they will be questioned to find out if they meet the inclusion criteria for the study. Inclusion and exclusion criteria are shown in Table 1.

**Table 1 pone.0312463.t001:** Inclusion and exclusion criteria.

Inclusion Criteria	Exclusion Criteria
Person aged 60 and over who belongs to the CRC at Concepción. Speak and read Spanish. Enabled and capable of approving the informed consent. Provide signed informed consent. Older adults who have a smartphone where they can run the audiobook mobile application. Older adults who are not participating in other emotional, social and/or motor training programs.	Significant psychiatric or medical illness (depressive disorder, delirium, intellectual disability, etc). Older adults classified with dependency criteria. Illiterate people. Presence of a severe sensory deficit, either in visual or hearing difficulties. Presence of neurodegenerative diseases (dementia, Alzheimer’s disease, Parkinson’s disease, multiple sclerosis, etc.).

If the older adults refuse to participate, they will be thanked and told there is no harm to them. Otherwise, they will be invited to a meeting at the CRC, on a schedule to be agreed.

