### Intervention

The intervention will consist of the use of the audiobook application for 4 weeks. During this period, the application will record the following data autonomously:

older adult id,date, hour and time that the older adult listened to each poem,poems listened.

This data will be stored locally and sent to a server for remote storage when the older adult has internet access.

Considering the hypothesis, there is no minimum application frequency of use to be suggested to participants. Thus, older adults should use the audiobook application according to their time availability and their motivation. Furthermore, participants are advised to abstain from any other emotional, social and/or motor training during the intervention period.

After two weeks of application use, the researchers ([name], [name], [name]) will carry out a follow-up in order to answer any questions that may arise from the use of the application, and explain again the objectives of the research, if necessary. This follow-up will be initially done by telephone, and in person if required.

After four weeks, the older adult will be invited to a meeting at the CRC, on a schedule to be agreed beforehand, to answer the well-being questionnaire (Part B) and a validated Spanish usability questionnaire (SUS [33, 34]).

Finally, data analysis will be carried out once the data gathering is finished.

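### A single-group before-after change is to be read as showing that listening to poems improves well-being, but the design has no comparator and the limitations do not say so

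*Protocol article*

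**What the plan says.** All references are to the protocol article.

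- **Hypothesis** (Objective, research question and hypothesis): "using a mobile application that allows listening to poems produces a positive change in older adults’ perception of well-being".
- **Reading of a positive result** (Results): if the hypothesis is confirmed, the finding is "that listening to audio of poems using a mobile application improves the perception of well-being of older adults". The section then looks ahead to other genres, more books and other populations. A comparison group is not among these extensions.
- **Design**: participants are their own comparison, "that is, a pretest/posttest with a single group".
- **Setting** (Recruitment): the open call goes to "all people over 60 years of age being treated at that place".
- **Contact during the intervention** (Intervention): at two weeks the researchers phone participants, or see them if required, to answer questions and "explain again the objectives of the research, if necessary". Technical support is also available (Discussion).
- **Exposure** (Intervention): there is no minimum frequency of use; participants listen as time and motivation allow.
- **Outcome** (Outcome measures): self-rated Likert items, Part A before and Part B after.
- **Analysis** (Statistical analysis): final well-being is regressed on initial well-being, frequency of use, usability, gender and other demographic variables.
- **Limitations of the study**: lost or damaged phones, battery, choice of genre, COVID-19 and reluctance to take part.

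**The concern.** The hypothesis and its planned reading are causal: app use produces the change, and listening improves well-being. The data will show only whether scores differ after four weeks. Several other things happen in those weeks to people who are attending a rehabilitation centre and are in touch with the research team. They rate their own well-being, and some may have had the study's aims explained to them again two weeks earlier.

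If the plan is followed as written, a significant change would be reported as an effect of listening, and further work on genres and populations would build on it. The data could not support that attribution however small the p-value. Readers would also find no warning in the section where they would look for one.

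**Working it through.** **1. Does any planned element separate listening from the rival explanations?**

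| Element | What it does | What it leaves open |
|---|---|---|
| Exclusion of people in other emotional, social or motor training (Table 1), and advice to abstain during the study (Intervention) | Reduces one kind of co-intervention | Care at the centre, time, researcher contact, expectation |
| App log and frequency-of-use covariate | Records how much each person listened | Use follows motivation and free time, so its slope can reflect who chooses to listen |
| Adjustment for initial well-being | Describes final score given initial score | Every participant has the app, so the model has no term contrasting access with no access |

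None of these supplies the missing contrast.

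**2. The plan's own sample size.** The Recruitment section sizes the study "to be able to reject the null hypothesis that the response difference is zero with power 0,8 and an error probability of 0,05", "considering a pre-post difference of 1,24 points on the mental health outcome" and "a potential standard deviation of 3,4". Take 3.4 as the standard deviation of the change and a two-sided test; the article states neither.

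n = [SD × (z₀.₉₇₅ + z₀.₈₀) / difference]² = [3.4 × (1.960 + 0.842) / 1.24]² = 59.01, rounded up to 60.

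The stated 60 is reproduced. (The exact t calculation gives 61, with power 0.794 at 60.) The number is right for what it sizes: a test that mean change is zero.

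**3. What that test does when listening has no effect.** This is an illustration; the drift sizes are assumptions.

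- Standard error = 3.4 / √60 = 0.439.
- Smallest significant mean change = t(0.975, 59 df) × 0.439 = 2.001 × 0.439 = 0.878 points.
- Assumed non-specific drift of 0.5 points (0.5/3.4 = 0.15 SD): noncentrality 0.5/0.439 = 1.14, rejection probability 0.20.
- Assumed drift of 1.24 points (1.24/3.4 = 0.36 SD): noncentrality 1.24/0.439 = 2.83, rejection probability 0.79.
- No drift: 0.05.

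The 0.79 is simply the design power, because the test responds to a shift of a given size whatever its cause.

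**4. Sensitivity to the meaning of 3.4.** If 3.4 is instead the standard deviation at one occasion, the SD of change is 3.4 × √[2(1 − r)], where r is the pre-post correlation.

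| r (assumed) | SD of change | Rejection probability, drift 0.5 | Rejection probability, drift 1.24 |
|---|---|---|---|
| 0 | 4.81 | 0.12 | 0.50 |
| 0.5 | 3.40 | 0.20 | 0.79 |
| 0.75 | 2.40 | 0.35 | 0.98 |

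**5. Would a larger sample help?** No. More participants make a given drift more likely to be significant without revealing its source.

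**The case against.** The design is openly labelled quasi-experimental, and the Design section gives ethical, contamination and feasibility reasons for it. The Results sentence is conditional and looks to future work; it sets no significance rule. The protocol limits competing training and logs listening. The arithmetic above concerns a test of mean change, whereas the Statistical analysis section names a regression, and the drifts are hypothetical. All of this stands. It means the fault lies in the causal wording and the silent limitations, not in concealment or in choosing a single group. The reasons given for not randomising do not license a causal reading.

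A reader might infer more than the documents support:

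- *That every participant hears the aims again at week 2.* The text makes this conditional on need.
- *That regression to the mean inflates the change.* Table 1 does not select on low or extreme well-being, and depressive disorder is excluded, so the documents give no mechanism for it.
- *That nothing at all guards against other explanations.* The training restrictions and the usage log are real, though partial.
- *That 0.20 or 0.79 is the study's false-positive rate.* These depend on assumed drifts; the documents give no estimate of drift, and 3.4 refers to a mental health outcome, not expressly to the authors' own questionnaire.
- *That a repeat baseline before use begins would supply the contrast.* Part A has 6 items and Part B has 12, and the article does not show that they are comparable. Baseline and installation share one meeting. A wait without app support could not separate attention or expectation.

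**Conclusion.** The concern holds as a point about inference. A single-group before-after study cannot support the conclusion that listening improves well-being, and the Limitations section omits the missing comparator. The rival explanations that rest on the protocol's own text are care at the centre, passage of time, researcher contact and expectation before a self-rated outcome.

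Their actual size is unknown. A non-specific drift well below the planning difference would already have a material chance of significance: about 0.20 at 0.5 points, or 0.12 to 0.35 over the readings of 3.4 tried above. This assumes no listening effect, 60 analysed participants and a two-sided test of mean change. The study can run as designed; its stated conclusion needs to change.

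**What to change.** 1. **Wording.** In the objective and hypothesis section and in Results, say that a positive result shows well-being changed over four weeks of access to the app, not that listening caused the change. Describe the frequency-of-use slope as an association. In Limitations of the study, add the missing comparator and name the rival explanations: care at the centre, time, researcher contact and expectation. This costs a few sentences and remains useful after data collection, because it governs how results are reported.

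2. **Week-2 contact.** In the Intervention section, limit this contact to technical help and drop the re-explanation of the research objectives. The small downside is that questions about the aims are answered only when a participant asks. This reduces one source of expectation but does not replace a comparator.

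A concurrent control would be needed to keep the causal claim, but it is a different study. Taking 1.24 as the between-group difference in change and 3.4 as its standard deviation, 2 × 59.01 = 118.02, or 119 per arm (238 in total), for 80% power. Splitting the planned 60 into 30 and 30 would give about 29%.
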